## Abstract

**Background:**

Bowel cancer is common and is a major cause of death. Meta-analysis of randomised controlled trials estimates that screening for colorectal cancer using faecal occult blood (FOB) test reduces mortality from colorectal cancer by 16%. However, FOB testing has a low positive predictive value, with associated unnecessary cost, risk and anxiety from subsequent investigation, and is unacceptable to a proportion of the target population. Increased levels of an enzyme called matrix metalloproteinase 9 (MMP-9) have been found to be associated with colorectal cancer, and this can be measured from a blood sample. Serum MMP-9 is potentially an accurate, low risk and cost-effective population screening tool. This study aims to evaluate the accuracy of serum MMP-9 as a test for colorectal cancer in a primary care population.

**Methods/Design:**

People aged 50 to 69 years, who registered in participating general practices in the West Midlands Region, will be asked to complete a questionnaire that asks about symptoms. Respondents who describe any colorectal symptoms (except only abdominal bloating and/or anal symptoms) and are prepared to provide a blood sample for MMP9 estimation and undergo a colonoscopy (current gold standard investigation) will be recruited at GP based clinics by a research nurse. Those unfit for colonoscopy will be excluded. Colonoscopies will be undertaken in dedicated research clinics. The accuracy of MMP-9 will be assessed by comparing the MMP-9 level with the colonoscopy findings, and the combination of factors (e.g. symptoms and MMP-9 level) that best predict a diagnosis of malignancy (invasive disease or polyps) will be determined.

**Discussion:**

Colorectal cancer is a major cause of morbidity and mortality. Most colorectal cancers arise from adenomas and there is a period for early detection by screening, but available tests have risks, are unacceptable to many, have high false positive rates or are expensive.

This study will establish the potential of serum MMP-9 as a screening test for colorectal cancer. If it is confirmed as accurate and acceptable, this serum marker has the potential to assist with reducing the morbidity and mortality from colorectal cancer.

## Background

Colorectal cancer is a major public heath problem: it is the third and second most common invasive malignancy in men and women, respectively, in England [1]. There are over 28000 incident cases in England and over 14000 deaths in England and Wales each year [1,2].

The five year age-standardised relative survival rate is less than 50% for men and women with cancer of the colon [3]. Survival is strongly associated with stage at presentation. The five-year relative survival rate for people with localised cancer is 90%, whereas the rate for those with distant disease is only 9% [4]. Most colorectal cancers arise from adenomas, and estimates of the progression rate suggest that there is a long window period for early detection by screening and removal of the adenoma [5]. Colorectal cancer, therefore, meets key Wilson and Jungner criteria for a condition that may be a suitable target for screening [6].

Meta-analysis of randomised controlled trials estimates that screening for colorectal cancer using faecal occult blood (FOB) test reduces mortality from colorectal cancer by 16% [7], but a low positive predictive value (12% for colorectal cancer) [8] means that most positive tests are false with associated unnecessary cost, risk and anxiety from subsequent investigation. Although a UK study is underway to assess whether flexible sigmoidoscopy screening can reduce the incidence and mortality of colorectal cancer, it will be several years before results show if incidence/mortality are reduced [9]. Early findings are promising, but only part of the colon is screened, the test is costly and invasive, and it has low acceptability: less than 50% of people aged 50–75 years accepted an invitation for screening [10]. Colonoscopy is the most accurate way to detect pathology, but it requires secondary care resources, is unacceptable to some, and has an element of risk. Combined results from several studies suggest that the incidence of perforation and haemorrhage in a diagnostic colonoscopy are 1 in 603 and 1 in 1352, respectively [11]. A study in the USA found a perforation rate of 1 in 510 within seven days of colonoscopy in people aged 65 years or older, although the rate was lower (1 in 747) where no indication, for example diverticulosis, was identified [12]. The cost, low acceptability and risk make colonoscopy unsuitable as a routine screening test.

FOB testing also has relatively low acceptability, with reported uptake rates in the UK of only 60% [13]. A blood test is likely to be a more acceptable routine screening test than FOB, flexible sigmoidoscopy or colonoscopy. Matrix metalloproteinases (MMPs) are proteolytic enzymes that are associated with tissue remodelling in normal and pathological processes [14]. Over-expression of MMPs has been correlated with progression in many tumour types, and over-expression of MMP-9 has been found in colorectal adenomas [15] and carcinomas [16,17]. A significant positive correlation has also been found between MMP-9 and the stage of colorectal tumours [18]. MMP-9 may be detected by ELISA assay.

### Pilot work

We have completed a pilot study of 300 patients (all "urgent" referrals) attending a specialist colorectal clinic. In this high prevalence group (27% with pathology), the accuracy of serum MMP-9 for colorectal neoplasia was 73% (sensitivity 99%, specificity 63%, positive predictive value 50%, negative predictive value 99%). Serum MMP-9, therefore, appears to have the potential to be a useful screening test for colorectal neoplasia. There is a strong possibility, however, that our pilot was affected by spectrum bias. Although the sensitivity and specificity of a test are unaffected by disease prevalence, the performance of a diagnostic test can vary according to the spectrum of the population being tested, that is the severity and clinical presentation of the disease [19,20]. Evaluation of the accuracy and acceptability of serum MMP-9 in a primary care population, the target population for a potential screening test, is required to inform the utility of serum MMP-9 screening in the general population.

*Feasibility work *for this study has also been undertaken. One hundred and ninety eight questionnaires were distributed in December 2003. There was a return rate of 74% (n = 146), and 59% (n = 116) returned a completed questionnaire. Twenty four respondents (21% of 116) had symptoms other than only abdominal bloating and/or anal symptoms, and 13 of these people (54% of 24) agreed to take part in the study. Eleven, of the 13 agreeing to take part, were invited to a general practice research clinic, eight returned the availability slip and seven agreed to attend. Six of these people attended a research clinic and all were eligible and consented to have a blood sample and colonoscopy.

Our pilot work suggests that serum MMP-9 is acceptable and has a high sensitivity and negative predictive value. Colorectal cancer is a suitable candidate for mass screening and a bowel cancer screening programme will be introduced in the UK with national coverage planned by 2010 [21,22]. Currently available screening tests (FOB, flexible sigmoidoscopy, colonoscopy) are, however, not particularly acceptable to the general population and are either risky or have high false positive rates. Flexible sigmoidoscopy or colonoscopy screening would also be expensive and place a considerable burden on existing resources. Serum MMP-9 is potentially an accurate, low risk and cost-effective population screening tool. It is, therefore, important that we evaluate its usefulness in a primary care population.

### Aims and objectives

#### Aim

To evaluate the accuracy of serum MMP-9 as a test for colorectal cancer in a primary care population.

#### Objective

Primary objectives are to evaluate:

(1) the accuracy of serum MMP-9 as a test for colorectal cancer by comparison with colonoscopy.

(2) the acceptability of serum MMP-9 as a screening test for colorectal cancer in a primary care population.

Secondary objectives are:

(1) to describe the prevalence of lower gastrointestinal symptoms in a primary care population.

(2) to assess the appropriateness of current referral guidelines.

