### Justification of sample size

All types of colonic polyps have potential for malignant change but this is more common with increasing size, a villous growth pattern and more severe dysplasia [25]. Increasing age, adenoma size and a villous component have been associated with risk for high grade dysplasia [26].

In the USA, 11% (n = 329) of 3121 people aged 50–75 years without symptoms of lower gastrointestinal disease who had a complete colonoscopy had advanced colonic neoplasia (adenoma with a diameter of at least 10 mm, or villous features, high grade dysplasia, or invasive cancer) [27]. If large tubular adenomas were excluded, about 6% (n = 155) of people had lesions. About 32% (n = 105) of the 329 people only had lesions proximal to the rectum and sigmoid colon.

In Norway, 13% (n = 25) of 193 people aged 62–73 years who were offered a colonoscopy or flexible sigmoidoscopy and had a full colonoscopy had a high risk adenoma (adenoma greater than or equal to 10 mm and/or villous components and/or severe dysplasia) [28]. About 39% (n = 11) of the 28 high risk lesions were not in the rectum or sigmoid colon. In the UK, high risk lesions (greater than or equal to three adenomas, a polyp greater than 1 cm, tubulovillous or villous histology, severe dysplasia, malignancy, or greater than or equal to 20 hyperplastic polyps) were found in 5% (n = 1905) of 40674 people aged 55–64 years who were screened using flexible sigmoidoscopy [9]. This will not include proximal lesions that could be found on colonoscopy.

Any test that might usefully be employed to screen for malignant or premalignant colorectal lesions should have a high sensitivity to minimise the false negative rate. Based on our pilot data and conservatively assuming a community prevalence of 6% [9,27,28]. a sample of 700 people would be sufficient to estimate sensitivity within 3% (95% confidence) and specificity within 4% (95% confidence). If the community prevalence of high risk lesions is greater than 6%, our estimate of sensitivity will have greater precision.

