### Methods of data analysis

#### Primary analysis

(1) ROC curve analysis will be undertaken to determine cut-off levels.

(2) Sensitivity, specificity, and positive and negative predictive values will be calculated with confidence intervals.

(3) The combination of MMP-9 level, symptoms, risk factors and socio-demographic status that best predict invasive and non-invasive colorectal neoplasia will be described.

(4) The acceptability of serum MMP-9 determination, FOB testing, flexible sigmoidoscopy and colonoscopy will be assessed by the initial questionnaire. The acceptability of serum MMP-9 determination and colonoscopy will also be assessed by a post-test acceptability questionnaire.

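### The primary objective is accuracy for colorectal cancer, but the 700 participants and the 3% precision for sensitivity are calculated for high risk lesions, so that precision does not apply to the objective

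*Protocol article*

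**What the plan says.** The Aim is "To evaluate the accuracy of serum MMP-9 as a test for colorectal cancer in a primary care population". Under Objective, primary objective 1 is to evaluate "the accuracy of serum MMP-9 as a test for colorectal cancer by comparison with colonoscopy". The Discussion draws its prospective conclusions in the same terms, as a test for colorectal cancer.

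Justification of sample size works with a wider target. It opens its argument with "Any test that might usefully be employed to screen for malignant or premalignant colorectal lesions should have a high sensitivity", and the calculation rests on "conservatively assuming a community prevalence of 6" per cent. The next sentence shows what that percentage refers to: "If the community prevalence of high risk lesions is greater than 6%, our estimate of sensitivity will have greater precision". From this and the pilot data the section concludes that 700 people will give sensitivity within 3% and specificity within 4%, each with 95% confidence.

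The pilot inputs (sensitivity 99%, specificity 63%) come from Pilot work, where "the accuracy of serum MMP-9 for colorectal neoplasia was 73" per cent. They are therefore for neoplasia, not for cancer.

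Under Primary analysis, items 1 and 2 (ROC cut-off, sensitivity, specificity and predictive values) name no target condition.

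**The concern.** A diagnostic accuracy study sized on sensitivity is sized on the number of people who have the target condition. If the objective names one condition and the calculation counts another, the promised precision belongs to the second. Here the counted group is wider than the one in the objective, so the objective will be answered with fewer cases than planned for.

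Two things are at stake. A headline about a test for colorectal cancer could carry a precision that was never calculated for cancer. And the 2x2 table, the ROC cut-off and the predictive values all depend on who counts as diseased, so the lesion group has to be settled before results are seen.

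**Working it through.** **Inputs.** N = 700, prevalence 6%, target half-widths 3% and 4% (Justification of sample size); sensitivity 0.99 and specificity 0.63 (Pilot work).

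**Step 1: reproduce the plan's figure.** Formula: 1.96 x sqrt(p(1 - p)/n), the usual large-sample (Wald) half-width.

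- Cases: 700 x 0.06 = 42. Non-cases: 700 - 42 = 658.
- Sensitivity: 1.96 x sqrt(0.99 x 0.01/42) = 3.01%.
- Specificity: 1.96 x sqrt(0.63 x 0.37/658) = 3.69%, which rounds to 4%.
- Cases needed for 3%: 1.96² x 0.99 x 0.01/0.03² = 42.26. Dividing by 0.06 gives 704.3, so 705 people against the stated 700.

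The arithmetic is sound. It is arithmetic for 42 people with high risk lesions.

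**Step 2: apply it to the stated objective.** The US definition quoted in the same section lists invasive cancer as one component beside several adenoma features. The UK definition likewise includes malignancy as one item among others, and the Norwegian one covers adenomas only. If 6% is the prevalence of the whole group, cancers number fewer than 42, and the half-width for cancer sensitivity exceeds 3%. No outside figure is needed for this.

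**Step 3: size of the shortfall.** The document gives no cancer prevalence, so the first column is an assumption. The half-width uses 99% sensitivity. The exact (Clopper-Pearson) lower limit when all n cancers are detected is 0.025^(1/n), with n rounded to a whole number. The last column is 42.26 divided by the prevalence.

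| Assumed cancer prevalence | Cancers in 700 | Wald half-width | Exact lower limit, all detected | People needed for 3% |
|---|---|---|---|---|
| 0.5% | 3.5 | 10.4% | 40% (4/4) | 8,452 |
| 1% | 7 | 7.4% | 59% (7/7) | 4,226 |
| 2% | 14 | 5.2% | 77% (14/14) | 2,113 |
| 3% | 21 | 4.3% | 84% (21/21) | 1,409 |

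The fair comparison for the exact limits is the exact limit at the planned 42 cases, not the 3%. With 42/42 detected it is 0.025^(1/42) = 92%.

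**Step 4: does the choice of lesion group matter within one cohort?** In the US study the same colonoscopies give 11% when large tubular adenomas count and a stated figure of about 6% when they do not. Applied to 700 people: 700 x 0.11 = 77 against 700 x 0.06 = 42. With 77 cases the half-width at 99% sensitivity would be 1.96 x sqrt(0.0099/77) = 2.2%. I use the percentages as the protocol states them; the count printed beside the 6%, 155 of 3,121, is 5.0%.

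**The case against.** The strongest defence is that cancer is screening shorthand. The Background explains that most cancers arise from adenomas and that screening works by finding and removing them, and the sample-size section speaks openly of premalignant lesions. On that reading the intended target was always the wider one. This makes the origin of the mismatch understandable, but the aim, objective and Discussion then claim more than the study is sized to show, and the wording still has to change.

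A second defence is that this is a condensed article and that the target for the ROC and accuracy analysis may be defined in the full protocol or analysis plan. That stands for the silence of items 1 and 2. It does not rescue the precision claim, because no later document can turn 42 high risk lesions into 42 cancers.

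Several stronger readings are tempting and are not supported:

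- A reader might infer that every label in the article conflicts with objective 1. The abstract's phrase "best predict a diagnosis of malignancy (invasive disease or polyps) will be determined" and Primary analysis item 3, "best predict invasive and non-invasive colorectal neoplasia will be described", describe the search for the best combination of predictors, not the accuracy of MMP-9. A wider outcome there does not contradict the objective.
- A reader might infer that the sample will contain only a handful of cancers. No cancer prevalence is given, the cohort is symptomatic, and people meeting urgent referral criteria stay eligible, so the upper rows of the table are not established.
- A reader might take the cited 5% to 13% as the effect of definition alone. Those studies also differ in procedure (sigmoidoscopy or colonoscopy), age range and country. Only the comparison within the US study isolates definition.
- A reader might infer that results could be reported against whichever definition looks best. That assumes the documents not shown are also silent, which cannot be known.

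**Conclusion.** The point holds. The stated primary objective is accuracy for colorectal cancer, and the stated precision is for high risk lesions. On the plan's own 6%, fewer than 42 cancers are expected, so sensitivity within 3% does not hold for objective 1. This rests only on the document's figures and on invasive cancer being a part, not the whole, of the lesion group.

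The size of the shortfall rests on an assumed cancer prevalence. From 0.5% to 3%, the half-width runs from about 10% down to 4%, and the best attainable exact lower limit from about 40% up to 84%, against 92% at the planned 42 cases. The 3% could apply to cancer only if cancer prevalence itself were about 6%, and then the 6% assumed for all high risk lesions would be too low.

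The 700 is not miscalculated. It answers a different question from the one the objective asks.

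**What to change.** - Name one primary target condition: high risk lesions, or advanced neoplasia including invasive cancer, with explicit size and histology criteria applied per person. Use it in the aim, objective 1, the ROC and sensitivity/specificity analysis, and the conclusions.
- In the sample size, use a prevalence that belongs to that same definition and restate the precision. If all adenomas of at least 10 mm count, the cited US figure is nearer 11% than 6%. State also which lesions the pilot's neoplasia covered, since its 99% is the sensitivity input.
- Report invasive cancer alone as secondary and descriptive, with its expected count and interval, and state that the 3% precision does not apply to it.
- Confirm that histology is recorded. The article mentions colonoscopy findings and results but does not describe histology collection.

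If the sponsor prefers to keep cancer as the primary target, the alternative is to state a cancer prevalence and re-size; the last column of the table shows the scale.

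Aligning the definitions is mainly a change of wording and a recalculation, provided histology is available. The downside is a narrower headline claim, about high risk or advanced lesions instead of cancer.

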## Methods/Design

### Study design

Community based survey with embedded diagnostic test accuracy evaluation. Accuracy of MMP9 will be assessed by comparison with the gold standard, colonoscopy. A cohort aged 50–69 years with lower gastrointestinal symptoms will be identified using a questionnaire. People who are willing to participate will be given further information at a general practice based research clinic and informed consent will be obtained. Participants will have a blood sample for serum MMP-9 determination and a colonoscopy.

### Recruitment of practices

Up to 30 general practices will be recruited. Practices will be eligible to participate if they are in the catchment area of University Hospital Birmingham NHS Foundation Trust.

### Eligibility criteria

People aged 50–69 years registered with participating general practices.

### Exclusion criteria

The GP will exclude people who are under investigation or treatment for colorectal cancer, unfit for colonoscopy, unable to give informed consent, or who should not be invited to take part, in the GPs opinion, for any other reason (e.g. recent bereavement, terminal illness or unable to give informed consent).

### Selection of participants

Lists of eligible persons will be generated from practice registers. These lists will be scrutinised by GPs, who will remove all patients deemed inappropriate to receive a questionnaire (according to criteria defined above).

A postal questionnaire will assess symptoms over the past three months, the acceptability of screening tests for colorectal cancer, risk factors for colorectal cancer, and willingness to take part in the study. The symptoms are based on the Department of Health (DoH) referral guidelines for suspected colorectal cancer [23,24]. One reminder will be sent two weeks later. Respondents who describe any colorectal symptoms (except only abdominal bloating and/or anal symptoms) and express willingness to take part in the evaluation will be sent an information leaflet and an invitation to attend a research clinic at their general practice.

GPs will be notified by fax of people who report symptoms that meet the criteria for urgent referral under the two week standard [24]. Such people will continue to be eligible for the study, although the GP will be made aware of their symptoms before the person is invited to a general practice based research clinic. Regular reports of symptoms (except abdominal bloating and anal symptoms) reported by all respondents will be provided to GPs. Reports of all people meeting the criteria for urgent referral and who decide not to fully participate in the study will be regularly provided to their GP.

### Informed consent

At the general practice clinic, the study will be fully described including potential benefits and risks, fitness for colonoscopy will be checked, and a basic medical history will be obtained. Informed consent will be sought and an appointment for colonoscopy will be arranged for those providing consent.

### Clinical evaluations, laboratory tests and follow-up

Colonoscopies will be performed in a dedicated research endoscopy facility based in the Wellcome Clinical Research Facility. Participants will be informed of the colonoscopy result on the day and the result will also be sent to their GP. Any participant found to have a malignancy will receive usual care. Two 5 ml blood samples will be collected immediately before the colonoscopy. One sample will be sent to the haematology laboratory for routine analysis (Hb, etc.), the other sample is for MMP-9 determination During transport this samples will be stored at 4°C. Serum will be stored at -80°C and the MMP-9 level will be determined on duplicate aliquots of each sample by ELISA assay. Participants will be flagged on the NHS Central Register to maximise the ascertainment of malignancy in those with no abnormality detected on colonoscopy.

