### Procedures for collecting and handling data

All data will be entered into a password-protected Access database and each participant will be allocated a unique study number. Access to the password-protected database will be restricted to core University of Birmingham staff working on this study, who are trained in policies and procedures related to confidentiality. The University is registered under the data protection act and university policies and procedures related to confidentiality will be followed.

Demographic details will be provided by the GP for eligible people aged 50–69 years. Data on symptoms, risk factors and the acceptability of screening tests for colorectal cancer will be collected using the recruitment questionnaire. Participants will also complete a bowel preparation acceptability questionnaire prior to colonoscopy and two post-test (colonoscopy) acceptability questionnaires (prior to discharge at 10 days subsequent to colonoscopy). Blood sample results and colonoscopy findings will be communicated to the study team using the unique study number and linked to patient records.

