### Bias and confounding

There will be duplicate determination of the serum MMP-9 level and dual data entry. Information on potential confounders, for example injuries or chronic illnesses that may lead to a raised serum MMP-9, will be collected at the general practice clinic. National and published data will be used to identify selection bias based on socio-demographic or symptom status. The analysis will be adjusted to take account of any confounders or selection bias. The blood sample for serum MMP-9 determination will be taken on the same day as the colonoscopy to improve comparability. All blood samples will be analysed in the same laboratory to ensure standardisation of measurement and reporting. The technician doing the MMP-9 ELISA assay and the clinician undertaking the colonoscopy will be blinded to the patient's symptoms as reported on the questionnaire.

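### Time-limited conditions that may raise MMP-9 are recorded at the GP clinic, not at the later visit where the blood is drawn, so the planned confounder adjustment can use out-of-date values

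*Protocol article*

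**What the plan says.** The relevant statements are spread over four Methods sections of the protocol article.

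- **Informed consent** (GP clinic visit): "Informed consent will be sought and an appointment for colonoscopy will be arranged for those providing consent". The colonoscopy is thus a later, separately booked visit. The interval is not given.
- **Bias and confounding** (covariates): "potential confounders, for example injuries or chronic illnesses that may lead to a raised serum MMP-9, will be collected at the general practice clinic". The same section says that the analysis will be adjusted for confounders.
- **Clinical evaluations, laboratory tests and follow-up** (marker): "Two 5 ml blood samples will be collected immediately before the colonoscopy". One tube goes for routine haematology and the other for MMP-9.
- **Bias and confounding** (reason for the timing): "The blood sample for serum MMP-9 determination will be taken on the same day as the colonoscopy to improve comparability".
- **Procedures for collecting and handling data** (existing form at the later visit): "Participants will also complete a bowel preparation acceptability questionnaire prior to colonoscopy".

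The article does not describe asking again about injuries or illnesses when the blood is taken.

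**The concern.** A covariate used to adjust a marker should describe the participant when the marker was measured. Here the marker is fixed to the colonoscopy day and the covariates to the GP clinic day. The first example the article gives of something that may raise MMP-9 is injury, which is time-limited. An injury after the clinic is missed, and one that has healed by the colonoscopy still counts as present.

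What is at stake is the confounder adjustment. If the recorded state differs from the state at the draw, the estimated association between these conditions and MMP-9 will tend to be too weak, and adjustment will remove only part of their influence. The same would hold for any description of which conditions produce a high MMP-9 in people without a lesion.

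**Working it through.** **1. The plan's own figure, to see whether this point touches it.** Inputs: N = 700 and prevalence 6% (Justification of sample size); pilot sensitivity 99% and specificity 63% (Pilot work).

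- Expected with lesions: 700 × 0.06 = 42. Expected without: 700 − 42 = 658.
- Half-width = 1.96 × √(p(1−p)/m).
- Sensitivity: 1.96 × √(0.99 × 0.01/42) = 3.01%, against the stated 3%.
- Specificity: 1.96 × √(0.63 × 0.37/658) = 3.69%, inside the stated 4%.

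The sample size reproduces. None of its inputs depends on when confounders are recorded, so it is unaffected.

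**2. Order of events.** GP clinic: confounders recorded, consent taken, colonoscopy booked. Later visit: bowel preparation questionnaire, blood draw, colonoscopy. That preparation precedes the draw is an inference, though a clear one, from the draw coming directly before the procedure.

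**3. What the gap does to a recorded condition.**

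| At GP clinic | At blood draw | Record used for adjustment |
|---|---|---|
| Present | Present | Correct |
| Absent | Absent | Correct |
| Present | Resolved | Counted although gone |
| Absent | New | Missed |

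Let *a* be the proportion of those recorded with the condition who still have it at the draw, and *b* the proportion of those recorded without it who still lack it. Suppose MMP-9 depends on the state at the draw and not otherwise on the state at the clinic. Then

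observed mean difference in MMP-9 = true difference × (a + b − 1).

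For a chronic illness *a* and *b* are both near 1, the factor is near 1, and little is lost. For an injury or acute illness *a* can be well below 1, and the factor falls with it. If clinic status said nothing about status at the draw, the factor would be 0. The article supplies neither *a* nor *b*, so no value can be calculated.

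**4. Scale, on an assumption.** If 5% to 10% of the lesion-free had a condition that began or resolved between visits, 0.05 × 658 = 33 to 0.10 × 658 = 66 records would be out of date. The rate is assumed.

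**5. Which analyses use the covariate.** Under Methods of data analysis, sensitivity, specificity and predictive values come from MMP-9 and the colonoscopy finding. The injury and illness items do not enter that table, so recording them at the wrong time cannot alter it. They enter only where the analysis is adjusted.

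**The case against.** **Chronic illness and the interval.** The article names chronic illnesses as well as injuries. Chronic illness seldom changes between two visits, and the interval may be short. This stands and limits the point to injury and acute illness.

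**Condensed article.** The full protocol may update these items at the endoscopy visit, and routine haematology is drawn with the MMP-9 sample. The first part is possible, but the article does state where the information is collected and describes no update. Haematology does not record an injury or illness history.

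**Specificity.** A reader might infer that this timing biases specificity. The documents do not support that. Injuries and passing illnesses also occur in people who are screened, and the false positives they cause belong in the specificity of a screening test. The 33 to 66 above cannot be set against the 4% precision, because they are covariate errors.

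**Bowel preparation.** A reader might also infer that blood taken after preparation puts the marker in a state a screening sample will not share, so that the cut-off will not carry over. The difference in setting is real, but nothing in the article says that preparation alters MMP-9, in which direction or by how much. On an assumed normal marker and an assumed common shift of +0.1 SD, specificity at a fixed cut-off would move from 63% to 59%; at −0.1 SD it would move to 67%. These figures show only that the result depends on an unknown input.

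**Moving the blood draw.** It is tempting to conclude that blood should be taken at the GP clinic. The Background does say that "there is a long window period for early detection by screening and removal of the adenoma", which suggests that a short gap changes adenoma status little. But the target includes invasive cancer and the participants have symptoms, so that statement does not settle the matter. Same-day sampling has a stated reason. Moving it would replace one collection site with up to 30 practices and produce MMP-9 results for people who never reach colonoscopy. That is a trade-off between designs and does not show the present choice to be an error.

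**Conclusion.** The point holds as a timing mismatch between covariate and marker, confined to time-limited conditions and to the adjusted analysis. It is a cheap improvement to a stated design choice. It is neither a contradiction in the text nor a demonstrated bias in the accuracy results.

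Its size is unknown. The direction, a weakened association and incomplete adjustment, rests on the assumption that MMP-9 responds to the condition present at the draw. The conclusion also assumes that no update of these items at the endoscopy visit exists in the full protocol.

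**What to change.** Keep the same-day blood draw. At the draw, repeat the items on recent injury, acute illness and current medication, for example alongside the questionnaire already completed before colonoscopy. State under Bias and confounding that the adjustment uses those answers for time-limited conditions; the GP clinic record can continue to serve for chronic illness. If the full protocol already does this, one sentence in the article is enough.

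When the cut-off is reported, note that the samples were taken at the colonoscopy visit, after bowel preparation, and that any effect of preparation on MMP-9 was not assessed.

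The cost is a few extra items on a form and their data entry. Sample size, visits and sample handling do not change.
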